### Outcome measures

Only participants with H_2_S ≥112 ppb, CH_3_SH ≤26 ppb and CH_3_SCH_3_ ≤ 8 ppb will be part of the research, which limits participation to individuals with halitosis caused by coated tongue alone. Immediately after treatment, a second halimetry test will be performed and the results will be analyzed.

### Hypothesis

Our null hypothesis is that there will be no change in halitosis following the use of PDT. Our experimental hypothesis is that there will be a reduction in halitosis following the use of PDT alone or in combination with a tongue scraper.

### Organization and statistical analysis of data

The Shapiro-Wilk test will be used to determine the distribution of the halimetricdata. If the data presents with normal distribution, analysis of variance (ANOVA) followed by the Tukey test will be used to evaluate the correlation between each of the proposed treatments and halitosis. The paired *t*-test will be used to compare the data before and after each treatment and determine whether the treatments reduced the degree of halitosis. The Kruskal-Wallis test followed by the Student-Newman-Keuls test will be used for data with non-normal distribution, and the Wilcoxon test will be used to analyze the data before and after each treatment. Microbiological data presents with log-normal distribution and will therefore be analyzed using the methods described for data with normal distribution. A significance level of α = 0.05 will be used.

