## Methods/Design

This study will be carried out in compliance with regulatory norms governing research involving human subjects. Approval was obtained from the Human Research Ethics Committee of University Nove de Julho (Brazil) under process number 037315/2013, and the study is registered with the United States National Institutes of Health (Clinical Trials.gov registration number: NCT02007993). The guardians of the participants will be informed regarding the procedures and will sign a statement of informed consent authorizing the participation of their sons and daughters in compliance with Resolution 196/96 of the Brazilian National Health Board.

Male and female adolescents enrolled at the dental clinic of the university will be recruited for the study. Those aged between 13 and 18 years, with a diagnosis of halitosis and OralChroma™ results of H_2_S ≥112 ppb during the cysteine challenge [11, 15, 39, 40] will be included. The exclusion criteria will be [41] dentofacial anomalies, currently undergoing orthodontic or orthopedic treatment, current use of a removable appliance, implant or dentures, periodontal disease, teeth with carious lesions, currently undergoing cancer treatment, diabetes mellitus, systemic (gastrointestinal, renal or hepatic disorder) conditions, ear, nose or throat conditions, respiratory conditions, antibiotic therapy in the previous month, current pregnancy [5] or hypersensitivity to the photosensitizer. As this is a randomized clinical trial, the recommendations of the Consolidated Standards of Reporting Trials (CONSORT) will be used to ensure greater transparency and quality (Figure 1).

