**Diagram of tongue scraper use.**

### Calculation of sample size

The error was established as , in which  and  are the means of groups 1 and 2. Assuming both samples as having the same size (n_1_ = n_2_), the sample size is obtained from the following equation:
1

in which  and  are the variances in groups 1 and 2, respectively. As more than two groups will be studied, the decision was made to employ the largest error found in the literature [54] to estimate the sample size. Assuming all groups as having normal or approximately normal distribution, and that the sample will be large enough for a significance level of α = 0.05, the *Z* value was determined to be 1.96. However, for the sample size, the test power was established as 1-β = 0.80. In case the hypothesis of normality in the samples was rejected, the sample size was corrected by 5%. Based on the experimental groups in the study by Tsai *et al*. [54] it was determined that each group should contain 26 participants (n = 26).

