## Discussion

The main objective of the proposed study is to evaluate the effect of PDT with and without the use of a tongue scraper for the treatment of halitosis in adolescents. This objective has two aspects: the evaluation of VSC levels before and after treatment through a quantitative analysis of H_2_S using GC, and a microbiological analysis of the effect of PDT on coated tongue. The findings are expected to provide convincing evidence that PDT is more effective for the treatment of halitosis.

In the literature, the treatment of halitosis is performed using a tongue scraper with or without a mouthwash [2], which leads to a small, long-term reduction in the amount of bacteria on the tongue [38]. Thus, daily oral hygiene is needed to maintain a low level of bacterial proliferation. As the penetration of light and spreading of the photosensitizer do not seem to be affected by the posterior papillae of the tongue, treatment with PDT is promising and may achieve satisfactory results, especially when combined with conventional treatment.

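### The hypothesis is tied to before-after tests within arms selected for high H2S, so a significant 'reduction' can arise without a PDT effect; the planned between-group test is sound but is not what decides efficacy

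*Protocol article*

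**What the plan says.** All references are to the protocol article.

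- **Hypothesis:** "Our null hypothesis is that there will be no change in halitosis following the use of PDT". The alternative is a fall in halitosis after PDT, alone or with the scraper. Neither statement names a comparator.
- **Organization and statistical analysis of data:** the paired *t*-test, or the Wilcoxon test if the data are not normal, is used to "compare the data before and after each treatment and determine whether the treatments reduced the degree of halitosis". The same section plans ANOVA with Tukey, or Kruskal-Wallis with Student-Newman-Keuls, across the three groups. It describes their purpose as evaluating the correlation of treatments with halitosis; the Abstract says that they compare groups. "A significance level of α = 0.05 will be used".
- **Methods/Design (eligibility):** entry needs "results of H_2_S ≥112 ppb during the cysteine challenge". Outcome measures repeats the threshold.
- **Abstract:** gas chromatography is used for diagnosis at the start of the study. **Outcome measures:** "Immediately after treatment, a second halimetry test will be performed". No separate baseline reading is described.
- **Table 1:** the arms are scraper, PDT, and scraper plus PDT. None is untreated or sham.
- **Discussion:** "The findings are expected to provide convincing evidence that PDT is more effective for the treatment of halitosis".

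**The concern.** Three features combine. The null concerns change within an arm, the test given the job of saying whether treatment worked is within-arm, and participants are chosen because the outcome variable was high. When people are selected on a high reading and that reading is kept as the baseline, the next reading is expected to be lower on average even if nothing is done. With no untreated arm, a paired test cannot separate that fall from a treatment effect.

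Group 3 has a further problem that needs no assumption about measurement error. Its participants also use the scraper, which the article itself treats as conventional therapy. A fall in group 3 counts towards the stated alternative even if scraping caused all of it.

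At stake is whether rejecting the stated null says anything about PDT. The expected conclusion, that PDT is more effective, is a comparison between arms. Paired tests cannot support it: a significant fall in one arm and a non-significant fall in another do not show that the arms differ.

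**Working it through.** The article gives no figure for this point, so there is none to reproduce. The check asks how often the paired test declares a reduction when PDT does nothing.

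**Inputs from the article**

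- Significance level 0.05. Sidedness is not worded, but in Calculation of sample size the *Z* "value was determined to be 1.96", which implies two-sided testing. The nominal chance of a false *reduction* is then 0.05 / 2 = 0.025.
- Arm size: the Abstract's 60 participants in three groups give 60 / 3 = 20 if equal; Calculation of sample size gives 26. Both were run.
- Selection: H2S ≥112 ppb.

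**Assumptions (not in the article)**

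- H2S on a log scale before and after is bivariate normal with equal variances and test-retest correlation ρ of 0.7 to 0.9.
- The qualifying reading is the 'before' value.
- The share of candidates above the cut-off is varied. The Background's 25% is a believed population prevalence of halitosis, so the top-quarter row is one scenario and not an estimate for this clinic.

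**Step 1: expected fall with zero effect.** In SD units of the unselected distribution, with the cut-off *c* SD from its mean:

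expected change = −(1 − ρ) × φ(c) / (1 − Φ(c))

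- Top 25%: φ(0.674) / 0.25 = 0.318 / 0.25 = 1.27. The fall is 0.3 × 1.27 = 0.38 SD at ρ = 0.7 and 0.1 × 1.27 = 0.13 SD at ρ = 0.9.
- Top 50%: φ(0) / 0.5 = 0.399 / 0.5 = 0.80. The fall is 0.24 SD and 0.08 SD.
- Top 75%: 0.318 / 0.75 = 0.42. The fall is 0.13 SD and 0.04 SD.

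**Step 2: chance of a significant reduction in one arm.** Simulated with zero treatment effect and a paired *t*-test at two-sided 0.05 (10,000 trials per setting; 4,000 for the top 75%).

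| Share passing the cut-off | n per arm | ρ = 0.7 | ρ = 0.8 | ρ = 0.9 |
|---|---|---|---|---|
| Top 25% | 20 | 0.60 | 0.43 | 0.23 |
| Top 25% | 26 | 0.72 | 0.53 | 0.30 |
| Top 50% | 20 | 0.28 | 0.20 | 0.12 |
| Top 50% | 26 | 0.35 | 0.25 | 0.14 |
| Top 75% | 20 | 0.10 | 0.08 | 0.05 |
| Nearly all (97.7%) | 26 | 0.035 | 0.029 | 0.028 |
| No selection | 20 | 0.027 at this n | | |

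The chance that at least one of the two PDT arms shows a false reduction, for the top 25% and n = 20, is 0.84 at ρ = 0.7 and 0.40 at ρ = 0.9.

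**Step 3: the planned between-group test under the same conditions.** One-way ANOVA across the three arms had a type I error of 0.044 to 0.055 in every setting, on post-treatment values and on change, at both arm sizes. Randomisation spreads the regression equally over the arms, so it cancels in the comparison.

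**The case against.** The strongest answer is that the randomised comparison is already in the plan. The analysis section names ANOVA with Tukey before the paired tests, and the Abstract says that it compares groups. A reader might infer that efficacy is judged only by before-after tests, or that nothing planned addresses the claim of greater effectiveness. The article does not support that: the Tukey or Student-Newman-Keuls contrasts do address it, and they are free of this bias. What remains is that the hypothesis names no comparator, the paired test is the one given the task of showing a reduction, and nothing says which result decides.

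Second, it is an inference that the qualifying reading is the baseline. It rests on diagnosis being made at the start of the study and on the post-treatment test being called the second. The full protocol may include a separate baseline reading, which would remove most of the regression. The inference is natural but not certain. The group 3 problem does not depend on it.

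Third, the high rates rest on an assumed correlation and on a population prevalence used as a clinic pass rate. The cysteine rinse supplies substrate for H2S, so more candidates may pass than 25%. This stands: the documents cannot fix the size.

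Fourth, participants are not selected on colony counts. Regression in the microbiological endpoint could arise only indirectly, through its correlation with H2S, and the figures above do not cover it.

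**Conclusion.** The concern holds in this form: followed as written, the plan can reject its stated null with no PDT effect, through regression to the mean in either PDT arm or through scraping alone in group 3. The direction is secure provided that the selecting reading is the baseline. The size is conditional. With 20 per arm and a correlation of 0.7 to 0.9, the false-reduction rate per arm runs from close to the nominal 2.5%, if almost every candidate passes the cut-off, to about 23–60% if only the top quarter do.

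A reader might go further and conclude that the trial cannot give a valid answer about PDT. The documents do not support that. The planned group comparison keeps its level and can show whether PDT differs from the scraper or adds to it. It cannot show an absolute effect of PDT, because no arm is untreated.

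**What to change.** 1. Restate the null as equality between arms in post-treatment H2S: PDT versus scraper, and PDT plus scraper versus scraper.
2. Test it with the between-group comparison already planned, preferably adjusted for the baseline H2S already collected (ANCOVA). The adjustment serves precision; the unadjusted comparison is already valid.
3. State that this comparison is the basis for efficacy conclusions, and label the paired *t* and Wilcoxon tests as descriptive.
4. Limit the conclusion to the effect of PDT relative to, or added to, the tongue scraper.
5. Say whether the qualifying reading is the baseline used in the analysis.

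The cost is rewording of the hypothesis, analysis and conclusion, with no new data. The sponsor gives up an absolute claim that PDT reduces halitosis, which this design cannot support.

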**Methods/Design:**

A quantitative clinical trial will be carried out involving 60 adolescents randomly divided into the following groups: group 1 will receive treatment with a tongue scraper, group 2 will receive photodynamic therapy applied to the posterior two-thirds of the dorsum of the tongue, and group 3 will receive combined treatment (tongue scraper and photodynamic therapy). Gas chromatography (OralChroma^TM^) and microbiological analysis will be used for the diagnosis of halitosis at the beginning of the study. Post-treatment evaluations will be conducted at one hour and 24 hours after treatment. The statistical analysis will include the Shapiro-Wilk test for the determination of the distribution of the data. If normal distribution is demonstrated, analysis of variance followed by Tukey’s test will be used to compare groups. The Kruskal-Wallis test followed by the Student-Newman-Keuls test will be used for data with non-normal distribution. Either the paired *t*-test or the Wilcoxon test will be used to compare data before and after treatment, depending on the distribution of the data.

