**Figure 1 Fig1:**
[figure not shown]
**Flowchart of study.** P = output power; E = energy and T = time in seconds.

The subjects selected will be randomly allocated to three groups (Table 1). All individuals will be submitted to evaluations with OralChroma™ before and after treatment.

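### Student-Newman-Keuls follows Kruskal-Wallis without saying whether it uses raw values or ranks, and under some readings its pairwise error can exceed 5% or its power can halve

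*Protocol article*

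**What the plan says.** In the protocol article, under Organization and statistical analysis of data, a normality test selects the analysis: "The Shapiro-Wilk test will be used to determine the distribution of the halimetricdata". The two branches have different follow-up tests.

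- Normal data: "If the data presents with normal distribution, analysis of variance (ANOVA) followed by the Tukey test will be used".
- Non-normal data: "The Kruskal-Wallis test followed by the Student-Newman-Keuls test will be used for data with non-normal distribution". The abstract repeats this.

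The level is fixed: "A significance level of α = 0.05 will be used". There are three arms. The abstract gives 60 participants, which is 20 per arm if equal; the sample-size section gives 26 per arm.

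Microbiological counts are sent to the normal-data methods, so SNK applies only to halimetric data that fail the normality test. The article does not say whether SNK is applied to raw concentrations or to ranks, or with which standard error. It gives no mean, SD or skewness for hydrogen sulfide.

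**The concern.** The plan leaves ANOVA because normality has failed. It then makes the pairwise decision with a procedure that, in its usual form, compares means against one pooled variance. With skewed concentrations the spread tends to grow with the level, so a variance pooled over three arms can be wrong for any given pair.

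The pairwise step is where scraper, photodynamic therapy and the combination are separated. If its standard error is too small, two equivalent arms are declared different more often than the stated 5%. If it is too large, a difference already detected by Kruskal-Wallis is lost. Rank forms of SNK exist, but they differ among themselves in the standard error, and the article names none of them.

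**Working it through.** **Inputs.** From the article: three arms, alpha 0.05, Z = 1.96 in the sample-size section, and n = 20 or 26 per arm. Assumed: log-normal data, two arms equal and the third shifted. The article has no error rate for SNK to reproduce; the benchmark is the stated 0.05.

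**Analytic check (large-sample).** Take the pair of equal arms at the last SNK step. If the variance used is r times the correct one, the real error is 2[1 − Φ(1.96√r)].

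*Raw values, pooled variance.* A shift of d log units multiplies the third arm's variance by c = exp(2d), so r = (2 + c)/3.

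| d (log units) | c | r | 1.96√r | error |
|---|---|---|---|---|
| −0.8 | 0.202 | 0.734 | 1.679 | 0.093 |
| −1.5 | 0.050 | 0.683 | 1.620 | 0.105 |
| limit, much lower | 0 | 0.667 | 1.600 | 0.110 |
| +0.8 | 4.953 | 2.318 | 2.984 | 0.003 |

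The ceiling is therefore about 11%, and it arises only when the differing arm is lower.

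*Joint ranks, n = 20.*

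- Span-dependent variance: the two-arm step uses 2n(2n+1)/12 = 136.7. With little separation the joint ranks actually vary by N(N+1)/12 = 305, so r = 0.448 and the error before the Kruskal-Wallis gate is 0.19. With full separation of the third arm, r = 1 and the error returns to about 0.05.
- Pooled rank mean square: with full separation the variances are 136.7, 136.7 and 35 (the last from n(n+1)/12). They pool to 102.8, so r = 0.752 and the error is 0.089.
- N(N+1)/12 throughout: with full separation r = 305/136.7 = 2.23 and the error is 0.003, which is conservative.

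**Simulation.** The grid had 10,000 runs per setting, log-SD 0.3 to 1.5, and shifts of 0.5 to 3 log-SDs in either direction. Every pairwise step was gated on Kruskal-Wallis at 0.05. Error on the equal pair:

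| Form | n = 20 | n = 26 |
|---|---|---|
| SNK, raw values | 0.000-0.105 | 0.000-0.107 |
| SNK, joint ranks, rank mean square | 0.037-0.087 | 0.041-0.089 |
| SNK, ranks, span-dependent variance | 0.058-0.156 | 0.056-0.165 |
| SNK, ranks, N(N+1)/12 | 0.003-0.039 | 0.004-0.042 |
| SNK, pairs re-ranked | 0.034-0.054 | 0.038-0.054 |
| Kruskal-Wallis, then pairwise Wilcoxon-Mann-Whitney | 0.037-0.054 | 0.041-0.054 |

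On raw values the error exceeded 0.057 in about 40% of settings, almost all with the differing arm lower. With all three arms equal (20,000 runs), familywise error was at most 0.046 for every SNK form.

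A separate run kept only data sets in which Shapiro-Wilk had rejected, at log-SD 0.5 to 1.0. It gave 0.05-0.11 on raw values with the third arm lower and 0.001-0.017 with it higher. The span-dependent form gave 0.10-0.16, rank-transformed values 0.045-0.072, the N(N+1)/12 form at most 0.046, and pairwise Mann-Whitney 0.04-0.06.

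**Power for a true difference, third arm 0.8 log-SD lower** (raw-value SNK against pairwise Wilcoxon-Mann-Whitney, ungated by Shapiro-Wilk):

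| log-SD | n = 20 | n = 26 |
|---|---|---|
| 0.3 | 0.54 vs 0.60 | 0.68 vs 0.73 |
| 0.5 | 0.48 vs 0.61 | 0.62 vs 0.74 |
| 1.0 | 0.26 vs 0.60 | 0.37 vs 0.74 |
| 1.5 | 0.12 vs 0.60 | 0.17 vs 0.74 |

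At log-SD 0.3, SNK on ranks gave 0.59 (n = 20), so the raw-value loss there is small on either comparison. Conditioning on Shapiro-Wilk rejection at log-SD 1.0 gave 0.26 against 0.63 (n = 20) and 0.38 against 0.75 (n = 26).

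**The case against.** The strongest reply is that none of these error rates belongs to the plan as written. The article fixes neither the form of SNK nor the distribution of the data, and some forms are sound: the N(N+1)/12 form and re-ranked pairs stay at about 5% or below. At a shift near 0.78 log-SD, roughly what n = 26 implies, SNK on rank-transformed values gave 0.047-0.054, and its power was close to that of pairwise Mann-Whitney (0.574 against 0.575 at n = 20, log-SD 1.0). On raw values, reversing the direction makes the error very small. The hypothesis section concerns change after photodynamic therapy, tested by paired methods and untouched by this. A condensed article may also leave the form of a test to the full plan.

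Most of this stands, and it rules out several stronger readings that a reader might draw:

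- That SNK in this branch has an error of 7-16%. That is a range of high values over forms and distributions the article does not specify.
- That no rank form helps. Two of them do.
- That three-arm SNK fails because of its stepwise logic. With equal variances it controls familywise error; the excess comes from the wrong pooled or span variance.
- That truly normal data never reach this branch. If Shapiro-Wilk were applied per arm at 0.05 and any rejection sufficed (an assumption), normal data would reach it with probability 1 − 0.95³ = 0.143.

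What does not stand is the claim that this is only missing detail. A specific test is named in two places. Its ordinary reading on means, and one rank-sum reading, both miss the stated 0.05 in plausible settings.

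**Conclusion.** The point holds in a conditional form. The article pairs a rank test with a follow-up that is ordinarily means-based, only for data already judged non-normal, and does not say how it is applied. Depending on the reading, the false-difference rate for two equal arms can reach about 11% (raw values, third arm lower) or about 16% (span-dependent rank sums). It is about 5-9% on rank-transformed values, and at or below 5% with the N(N+1)/12 variance or when all arms are equal. Raw-value power can fall by half or more when log-SD is about 1 or higher and the differing arm is lower; the loss is small at log-SD 0.3.

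These sizes rest on assumed log-normal data and assumed shifts. The reading range of 0 to 2913 ppb leaves room for right skew, but the article gives no figure that settles it. The conclusion is the same at 20 and 26 per arm. The wording should be changed before analysis, since the change is simple and removes the dependence on an unstated form.

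**What to change.** In the abstract and under Organization and statistical analysis of data, replace the words that introduce SNK with: *followed, if Kruskal-Wallis is significant at 0.05, by pairwise Wilcoxon-Mann-Whitney tests each at 0.05*.

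With exactly three arms, two pairwise equalities can be true together only if all three arms are equal, and Kruskal-Wallis tests that hypothesis. The procedure is therefore closed and needs no further adjustment. In the simulations its error on the equal pair was 0.037-0.054, with power of about 0.60 (n = 20) and 0.74 (n = 26) at a shift of 0.8 log-SD.

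Dunn's test with Bonferroni is also valid but less powerful (about 0.48 and 0.62). If the sponsor prefers to keep SNK, the text should name a rank form and its standard error that hold 5%, such as N(N+1)/12 or re-ranked pairs.

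The cost is one phrase in two places, with no added patients, visits or measurements. Compared with the span-dependent form, some apparent power is given up (0.78 against about 0.74 at n = 26), but that form's advantage comes with its excess false positives.
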